### Previous research on CCMM

Research on CCMM has investigated several chronic diseases, like cancer, arthritis, cardiovascular disease or hypertension, chronic pain, type 2 diabetes mellitus (T2DM) [15] and depression [16]. Most of them are physical conditions, as mental diseases often lead to impaired cognition and communication barriers that make couple collaboration challenging to develop [11]. Physical health conditions that have long disease courses are susceptible to lifestyle and psychosocial interventions, and thus are suitable for CCMM [11, 17]. Intervention strategies employed by previous research fall into three broad categories [15]: couple-based health education, communication promotion, and behavior change training. These three strategies also have been implemented conjointly [15, 16] in the intervention group of no less than two pairs of couples, over 3 to 20 telephone or in-person courses, with comparison to a patient-only group with or without health education. The follow-up period ranges from 1 to 12 months.

So far, CCMM on chronic diseases management has been shown to improve patients’ depressive symptom [16], but its effects are not conclusive regarding couples’ behavior [10], patients’ physical condition [18], or spouses’ health status [6, 15]. There are few CCMM studies on T2DM. We found a total of five randomized controlled trials (RCT) on CCMM with diabetes. Although a positive ripple effect between couples on weight loss was found by Gorin and colleagues [19], the series of studies by Trief showed neither statistically-significant difference in blood glucose control among patients [20] nor significant changes in diet or physical activity levels of their spouses [21]. Another early RCT by Wing and colleagues suggested that the effect of CCMM may be gender-specific, such that female but not male diabetes patients were more like to lose weight if treated with their partners than treated alone [22]. To better evaluate the effects of CCMM, studies equipped with theory-driven interventions and outcome measures targeting at both the patients and their spouses are needed [6, 10, 15].

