### Sample size

The sample size calculation was based on the primary hypothesis that the couple-based intervention would result in a 0.5% more reduction in HbA_1c_ as compared to the individual-based intervention over 12 months. This difference in HbA_1c_ is interpreted as a clinically meaningful change in glycemic control [23, 24]. A sample size of 194 couples (97 couples per arm) would provide 80% power to detect a between-arm difference of this magnitude (standard deviation (SD) =1.5%) for a longitudinal design with three repeated measures having an autoregressive covariance pattern, assuming the correlation between observations on the same subject of 0.5 [25], *α* of 0.05, and a 10% dropout rate.

The proposed sample size also satisfies the power requirement for subgroup analyses among male patients and patients with baseline HbA_1c_ ≥ 8.0%. These two subgroup analyses were chosen, considering the traditional female-dominated role in meal preparation and caregiving [26]; and a more evident reduction in HbA_1c_ among those with worse baseline glycemic control [20]. In light of previous couple-based T2DM interventions [20, 27, 28], it is assumed the ratio of male vs female patients enrolled would be around 1.2, resulting in 106 male participants available for subgroup analysis. With *α* of 0.05 and an auto-correlation of 0.5, the study will have over 90% power to detect a between-arm difference of 0.6% in HbA_1c_ (SD = 1.1%). Similarly, for the subgroup of patients with HbA_1c_ ≥ 8.0% (assuming *n* = 64, 33% of the whole sample), our study will have 90% power to detect a between-arm difference of 0.7% in HbA_1c_ (SD = 1.1%). Sample size and power calculation were conducted by PASS 11, using two independent means with repeated measures procedure [29] .

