#### Statistical considerations

Descriptive analyses comparing couples’ baseline characteristics between the intervention and control arms will be performed to assess the balancing of the group assignment. The intention-to-treat (ITT) approach will be applied to examine the treatment effects in accordance with the original randomization assignments. Missing baseline covariates and missing outcomes will be multiply imputed under missing at random assumption and separately by treatment arms [51].

The multilevel linear mixed modeling (MLM) will be employed to evaluate repeat measures of participants over time, while accounting for variations between community health care centers (blocks). The longitudinal changes of patients’ HbA_1c_ within- and between- treatment arms over 12 months will be examined, and the treatment effect is estimated as the differences between the within-arm changes from baseline to follow-up between the two intervention arms. MLM will be also applied to other continuous outcomes with one or more repeat measures, adjusted for time, study arm, a time and study arm interaction, and baseline covariates. The treatment effect will be further examined in two subgroup analyses, stratified by gender and patients’ baseline glycemic levels. All analyses will adjust for baseline sociodemographic covariates and functional states that are statistically-significantly different between treatment arms, and empirically-suggested as strong predictors for the outcomes.

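### Gender and baseline-HbA1c questions about differences in effect are planned and powered as separate within-stratum tests, which cannot establish a difference

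*Protocol article*

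**What the plan says.** Under Statistical considerations: "The treatment effect will be further examined in two subgroup analyses, stratified by gender" and by baseline glycemic level. The only interaction named there is in the general model specification, "adjusted for time, study arm, a time and study arm interaction, and baseline covariates". That term carries the treatment effect itself and says nothing about whether the effect differs between subgroups.

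Under Sample size: "The proposed sample size also satisfies the power requirement for subgroup analyses among male patients and patients with baseline" HbA1c of 8.0% or more. The calculations are within-stratum comparisons of the arms: 106 men, difference 0.6%, SD 1.1%, power over 90%; and 64 patients with HbA1c of 8.0% or more, difference 0.7%, SD 1.1%, power 90%.

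The same section justifies the two subgroups by women's traditional role in cooking and caregiving, and by "a more evident reduction in HbA_1c_ among those with worse baseline glycemic control". The background section adds that one early trial suggested "the effect of CCMM may be gender-specific"; that result concerned weight loss.

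**The concern.** Each justification is a statement that the effect is larger in one stratum than in the other. The quantity that answers it is the difference between the two stratum effects, with its own standard error. A test within men alone, or within HbA1c of 8.0% or more alone, does not estimate that quantity. Two separate p-values, one below 0.05 and one above, are also weak evidence of a difference, because strata of this size often disagree by chance.

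At stake is how the subgroup results are read. The trial is meant to yield a management model for community use, and a false impression that it helps only one sex, or only patients on one side of an HbA1c threshold, could misdirect its use. The stated 90% powers may also reassure readers about a question to which they do not apply.

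**Working it through.** **Inputs (Sample size section).** Overall effect 0.5%, SD 1.5%, three measures, AR(1) with correlation 0.5, α 0.05 (taken as two-sided), 10% dropout, 97 per arm. Subgroups: 106 men, hence 194 − 106 = 88 women; 64 with HbA1c ≥ 8.0%, hence 130 below. The arms are assumed equal within each stratum.

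**Reproducing the plan's figures.** Variance factor for the mean of three AR(1) measures: [3 + 2(2 × 0.5 + 0.25)]/9 = 0.611. Variance = 2.25 × 0.611 = 1.375. n per arm = 2(1.96 + 0.842)² × 1.375/0.5² = 86.3, so 87; 87/0.9 = 96.7, so 97 per arm and 194 in total, as stated. With SD 1.1% and no dropout, 53 men per arm and 0.6% give 94.9% power (stated: over 90%); 32 per arm and 0.7% give 90.3% (stated: 90%).

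**One common effect of 0.5%, SD 1.5%, 10% dropout.** SE in a stratum = √(2 × 1.375/n per arm).

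| Stratum | n per arm | SE | Power |
|---|---|---|---|
| Men | 47.7 | 0.240 | 55% |
| Women | 39.6 | 0.264 | 48% |
| HbA1c ≥ 8.0% | 28.8 | 0.309 | 37% |
| HbA1c < 8.0% | 58.5 | 0.217 | 64% |

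Probability that exactly one stratum is significant = p₁(1 − p₂) + p₂(1 − p₁):
- Gender: 0.549 × 0.525 + 0.475 × 0.451 = 0.288 + 0.214 = 50%. Men only: 29%.
- HbA1c: 0.366 × 0.365 + 0.635 × 0.634 = 0.134 + 0.403 = 54%. HbA1c ≥ 8.0% only: 13%; below 8.0% only: 40%.

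**Sensitivity (10% dropout throughout).**

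| Assumption for the common effect | Gender | HbA1c |
|---|---|---|
| 0.5%, SD 1.5%, time-averaged | 50% | 54% |
| 0.5%, SD 1.1% in the named subgroup, pooled SD kept at 1.5% (1.87% in women, 1.66% below 8.0%) | 60% | 49% |
| 0.5%, SD 1.1% in all strata | 35% | 43% |
| 0.5%, SD 1.5%, change from baseline to 12 months | 37% | 38% |
| 0.6% (gender) or 0.7% (HbA1c), SD 1.1% in all strata | 18% | 13.5% |

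For the change row, baseline and 12 months are two AR(1) steps apart, so the correlation is 0.25 and the variance is 2 × 2.25 × (1 − 0.25) = 3.375. The powers are 26% and 23% for men and women, and 18% and 31% for HbA1c ≥ 8.0% and below.

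**Interaction test.** By construction it declares modification in 5% of trials when the effect is homogeneous. At SD 1.5%, SE = √(2.75/47.7 + 2.75/39.6) = 0.357 for gender and √(2.75/28.8 + 2.75/58.5) = 0.377 for HbA1c. Power for a 0.5% difference between strata is 29% and 26% (48% and 44% at SD 1.1%). The difference detectable with 80% power is 2.80 × SE, about 1.00 and 1.06 HbA1c points (0.73 and 0.78 at SD 1.1%). For 0.6% in men against zero in women, power is 39% at SD 1.5% and 63% at SD 1.1%.

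**The case against.** The article is condensed and its SAP is not shown. It does not exclude an interaction test, and it states no rule that significance in one stratum and not the other shows effect modification. A reader might infer that the investigators have committed to that reading; the text does not support this. It is also legitimate to ask whether the intervention works among men, or among poorly controlled patients. The subgroups are only two, prespecified and justified, and gender is a randomization stratum.

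The size also needs care. A reader might conclude that a homogeneous effect would look subgroup-specific half the time whatever the inputs. That holds only for a common effect near 0.5% with SD 1.5% and the time-averaged formula, whereas Statistical considerations describes differences in change from baseline. The 50% and 54% also count discordance in either direction. For HbA1c, most of it (40 of 54 points) is significance only below 8.0%, the reverse of what the protocol expects. The background gender finding is weak support, since it concerns weight loss in women and the powered subgroup is men.

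All of this limits the claim. What stands is that the article does fix a method (stratified analyses) and a power target (within stratum), and both are mismatched to the reasons it gives. That is a stated choice, not a detail left out.

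**Conclusion.** The concern holds in a bounded form. The within-stratum tests can answer whether there is an effect in men or in HbA1c ≥ 8.0%; they cannot answer whether the effect differs by gender or baseline control, which is what the rationale asks. Under a common 0.5% effect, discordant strata would be expected in 50% and 54% of trials at the primary inputs, and in about 35% to 60% across the other SDs and the change-from-baseline estimand. It falls to 13.5% to 18% only if the larger subgroup effects held for everyone with SD 1.1% throughout, and that SD conflicts with the overall 1.5%. The specific patterns of men only (29%) and HbA1c ≥ 8.0% only (13%) are less frequent than the totals but above the 5% of an interaction test.

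The figures assume equal arms within strata and independent stratum tests. The primary comparison is unaffected. The 8.0% cut-point is secondary: it appears in the power section, while the analysis section speaks only of baseline glycemic levels.

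**What to change.** In the mixed model on all patients, add an arm-by-gender-by-time term and, in a separate model, an arm-by-baseline-HbA1c-by-time term, with HbA1c preferably continuous. Base any claim of effect modification on the interaction estimate and its 95% confidence interval. Report both strata of each factor descriptively, with intervals. State that the 90% powers refer to effects within a stratum, and that interaction power is low: about 26% to 29% for a 0.5% difference at SD 1.5%, and 44% to 48% at SD 1.1%, on the time-averaged scale.

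The cost is a few sentences and the added model terms; no extra patients, visits or measurements are needed. The downside is that subgroup claims become more cautious, and a real but moderate difference will often remain unproven.

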### Randomization and allocation concealment

Participants of each community health center will be randomized 1:1 within center into a couple-based arm (intervention) and an individual-based arm (control). To better balance key covariates, stratified randomization by patients’ gender and age group will be performed by a statistician otherwise not involved in the project using STATA 15. The order of which arm receiving each education session first will also be randomized, to ensure that the treatment sequence is equivalent between arms. Other than the statistician, all the research staff and community health workers will not know the group allocation prior to the education session. The community health workers designated as the care managers will call the participants to inform them of their group allocation, and to schedule the first session.

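### Adjustment covariates are chosen partly by baseline significance tests and, separately, the HbA1c effect is not conditioned on baseline: fix the covariate set and the effect definition

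*Protocol article*

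**What the plan says.** The last sentence of Statistical considerations sets the covariate rule: "All analyses will adjust for baseline sociodemographic covariates and functional states that are statistically-significantly different between treatment arms". It does not stop there. It goes on, after an *and*, to covariates that existing evidence marks as strong predictors of the outcomes. The text does not say whether a covariate must meet both conditions or only one, and it names no covariates.

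The Randomization and allocation concealment section says "Participants of each community health center will be randomized 1:1 within center", and that stratified randomisation by patients' "gender and age group will be performed by a statistician otherwise not involved in the project". Its stated purpose is better balance on key covariates.

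Statistical considerations also says that the mixed model accounts for variation between centres. It defines the HbA1c treatment effect as the between-arm difference in the within-arm changes from baseline to follow-up. Table 2 schedules HbA1c at baseline, month 6 and month 12, so baseline enters the primary analysis as part of the outcome.

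**The concern.** In a properly randomised trial a baseline difference between arms is chance. A significance test therefore says nothing about whether a covariate matters for the outcome, and it is not a sound rule for choosing model terms. Two consequences follow.

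- The primary model cannot be written down until the arms have been compared at baseline. The rule covers all analyses, so this applies to both primary outcomes, patient HbA1c and spouse SF-36.
- The rule works against the design. Gender and age group are balanced by stratification, so they are the variables least likely to pass a test for imbalance.

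A second matter sits in the same section but in a different sentence. An effect defined as a difference in change, with no conditioning on baseline, is less precise than a baseline-adjusted effect when the correlation between visits is moderate, as the sample size section assumes.

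**Working it through.** **Inputs (Sample size section).** The target between-arm difference in HbA1c is 0.5 percentage points. The SD is 1.5, and three repeated measures are taken to follow an AR(1) pattern with ρ = 0.5. Dropout is 10%, and α = 0.05 (two-sided assumed; the text does not say). The stated result is "A sample size of 194 couples (97 couples per arm) would provide 80% power".

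**1. The plan's own figure.** For the mean of three AR(1) measures with ρ = 0.5, the variance factor is f = [3 + 2(0.5 + 0.5 + 0.25)]/9 = 0.611.

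- n per arm = 2 × (1.96 + 0.842)² × 1.5² × 0.611 / 0.5² = 86.3, so 87.
- 87/0.90 = 96.7, so 97 per arm and 194 in total.
- Power at 87 per arm is 80.3%.

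The stated size is reproduced, so the checks below use 87 evaluable per arm.

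**2. Which covariates the rule would select.** Simulation with 2,000 trials per scenario, 174 evaluable patients and randomisation in blocks of 4 within centre, gender and age group. Assumed, not in the documents: 10 centres, two age groups, and gender plus age explaining 10% or 20% of HbA1c variance.

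- Gender or age group differed significantly between arms in 0 to 0.05% of trials. If both conditions are required, these factors almost never enter.
- Under the *either* reading, consider four unstratified baseline measures from Table 2 (education, retirement status, C-MMSE, CES-D). If they are independent and each is tested at 0.05, the chance that at least one enters by p-value alone is 1 − 0.95⁴ = 0.185.

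**3. What omitting gender and age does** (same simulation; Monte Carlo standard error about 0.5 points for a 5% rate).

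| Analysis of the month 6/12 mean | Type I error, factors omitted | Power, omitted vs included (10% of variance) | Power, omitted vs included (20%) |
|---|---|---|---|
| Change from baseline | 4.9% to 5.9% (5.0% to 5.7% when included) | 64.5% vs 63.9% | 67.5% vs 67.8% |
| Baseline-adjusted | 4.4% to 4.8%; 3.3% if factor effects grow by half after baseline | 82.9% vs 84.6% | 84.4% vs 88.0% |

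For change, at 10% of variance and no treatment effect, the model standard error was 0.215 against an empirical 0.217. A factor effect that is constant over time cancels within each patient. That is also why simulated power for change exceeds the 59% in step 4: total SD is held at 1.5, and the part due to the factors drops out.

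**4. Change against baseline adjustment.** Power = Φ(0.5 / (1.5 × √(2f/87)) − 1.96), where f is the variance factor of each estimator. For the mean of months 6 and 12 under AR(1), the variance of the follow-up mean is (1 + 0.5)/2 = 0.75 and its covariance with baseline is (0.5 + 0.25)/2 = 0.375.

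- Change: f = 1 + 0.75 − 2 × 0.375 = 1.00; standard error 0.227; power 59%.
- Baseline-adjusted: f = 0.75 − 0.375² = 0.609; standard error 0.178; power 80%.

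Sensitivity to the time point and the correlation pattern:

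| Setting | Change: f, power | Baseline-adjusted: f, power |
|---|---|---|
| AR(1), mean of months 6 and 12 | 1.00, 59% | 0.609, 80% |
| AR(1), month 12 only | 2 − 2 × 0.25 = 1.50, 43% | 1 − 0.25² = 0.9375, 62% |
| All correlations 0.5, mean of months 6 and 12 | 1 + 0.75 − 2 × 0.5 = 0.75, 72% | 0.75 − 0.5² = 0.50, 87% |
| All correlations 0.5, month 12 only | 2 − 2 × 0.5 = 1.00, 59% | 1 − 0.5² = 0.75, 72% |

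The nearness of 0.609 to the 0.611 of step 1 is a coincidence, since the two factors describe different estimators. In practice, though, baseline adjustment delivers about the promised power and the described change analysis does not.

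**The case against.** The best defence has four parts.

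- **The rest of the sentence.** If *and* joins two groups of covariates, strong predictors enter whatever the test shows, and these could include gender and age. This stands as far as it goes: a reader might infer that the stratification factors are certain to be left out, and the text supports that only if both conditions are required. But the *either* reading still admits variables because of chance imbalance, and the predictors remain unnamed.
- **Safeguards.** Centre, a randomisation factor, is already in the model. The Study measures section keeps data analysts blinded throughout, so the choice could not easily be steered towards one arm. Both are true. Neither makes the covariate set fixed, because the selection still compares arms.
- **Standard errors.** A reader might infer that the rule gives wrong standard errors or an invalid test. The documents do not support that. For the planned difference in change, omitting gender and age makes almost no difference; in a baseline-adjusted analysis the test is correct to mildly conservative.
- **Baseline HbA1c.** A reader might infer that the significance filter drops it. It does not: HbA1c is neither a sociodemographic covariate nor a functional state, and it enters through change from baseline. Nor does a fall from 80% to about 72% describe this trial. That figure belongs to a comparison of follow-up values with baseline left out, or used only when significant, which the protocol does not plan. The power loss that does exist comes from the effect definition, and deleting the covariate rule alone would not recover it.

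**Conclusion.** The point holds in two distinct parts.

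First, the protocol makes baseline significance a criterion for covariate choice in all analyses, with an ambiguous link to a second criterion. On either reading the primary model depends on the realised data. This is a flaw of prespecification with little numerical effect: no inflation of type I error, about no power cost for a difference in change, and about 2 to 4 points in a baseline-adjusted analysis. Those sizes rest on the assumed number of centres, two age groups and 10% to 20% of variance explained.

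Second, and separately, estimating the HbA1c effect as an unconditioned difference in change gives about 59% power against about 80% with baseline adjustment. This rests on the plan's AR(1) correlation of 0.5, 87 evaluable per arm, a two-sided test and the mean of months 6 and 12. Across the four settings checked, the gap is 13 to 21 points, always in favour of baseline adjustment.

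**What to change.** Change two sentences in Statistical considerations.

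- **Covariates.** Delete the significance criterion, which also removes the ambiguous *and*. Name gender and age group (as used in randomisation) as fixed terms, keep centre in the model, and list any other prognostic covariates before unblinding. Keep the baseline comparison descriptive, without p-values.
- **HbA1c effect.** Estimate it conditional on baseline. Use either a longitudinal model with baseline means constrained to be equal across arms, or an ANCOVA-type mixed model of the month 6 and month 12 values with baseline HbA1c as a covariate. Do not add baseline as a covariate while it also remains an unconstrained repeated response: that uses it twice and leaves the difference-in-change effect in place.

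The only cost is a text change. All the variables are already collected.

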#### Implementation evaluation

The study implementation will be evaluated in reference to the Reach, Effectiveness, Adoption, Implementation, and Maintenance (RE-AIM) framework [52, 53]. Tailored to the present study (Table 3), Reach will be revaluated by participation rate, and representativeness of participants. Effectiveness will be indicated by the health outcomes listed in Table 2 above; and Maintenance at the participants level will be measured as these treatment effect for long term (i.e. 1 year).

**Table 3 Tab3:** Reach, Effectiveness, Adoption and Implementation (RE-AIM) framework indicators

Domain	Indicators	Source	Data Collection Tool
**Reach**	Participation rate	Participants & Disease management system	Enrolled couples /all couples being contacted
	Representativeness		Enrolled couples / all eligible couples registered in the system
**Effectiveness**	Health outcomes	Participants	HbA_1c,_ Quality of life, BMI, WC, blood pressure, fasting glucose & lipid profile; management and healthy behaviors (exercise, diet)
**Adoption**	Number of health workers who prefer couple-based over individual-based interventions	Community health workers	Qualitative interview and survey of community health workers
**Implementation**	Treatment fidelity	Randomly selected taped sessions	10% of taped sessions randomly selected and reviewed by an expert panel, against the full detailed intervention manuals for adherence and quality.
	Participant involvement	Participants	Course registration forms recording attendance rate
	Participant satisfaction	Participants	Satisfaction questionnaire on the program, from 1 (strongly disagree) to 4 (strongly agree).
	Incremental cost- effectiveness ratio (ICER) of the intervention and control arms	Participants	ICER = ∆C/∆E = (C_intervention_ − C_control_)/ (E_intervention_ – E_control_); C is the program and labor costs; E is effectiveness defined as the percentage of patients whose HbA_1c_ is lower than 7%
**Maintenance**	Effectiveness over 1 year	Participants	Same as effectiveness.

Adoption by the community health workers will be calculated as the number of them who prefer the couple-based intervention than the individual-based intervention over total number of care providers conducting the interventions.

Implementation will be examined by treatment fidelity, participant involvement and satisfaction with the program, and cost-benefit. Treatment fidelity will be evaluated by an independent expert of behavior medicine, who will randomly select 10% of the taped sessions and evaluate them against the fully detailed intervention manuals for adherence (whether contents are being presented as intended) and quality (how well sessions are being delivered). Participant involvement will be measured by the attendance rate. Participants’ satisfaction with intervention will be evaluated by the degree to which they agree with a series of statements, on a scale from 1 (strongly disagree) to 4 (strongly agree) (Additional file 3). The cost-benefit will be measured as the incremental cost-effectiveness ratio (ICER) between the intervention and control arms. The ICER is calculated as the difference in program and labor costs divided by the difference in effectiveness of the two treatment arms, whereby effectiveness is defined as the percentage of patients reached HbA_1c_ < 7%.

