### Recruitment

For participant recruitment, community health care centers will first identify all potentially eligible participants from their case management system. Community nurses will contact these patients and their spouses to inform them about the study by phone or in person when patients visit the centers. In addition, awareness campaigns and publicity will be conducted at the centers, through onsite posters, publicity materials and advertisements broadcasted on the centers’ website and WeChat accounts.

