### Strengths & limitations

The development of the couple-based collaborative management model is based on theoretical framework, the latest clinical guidelines and the needs of old couples and community health workers. The model validation uses a randomized controlled trial design under strict quality control and makes thorough effect evaluation regarding its effects on the patients, their spouses and the whole implementation process. Our study will be conducted at the community health care centers that have established stable doctor-patient relationships with the elderly dwellers. This solid patient foundation will facilitate our participant recruitment and follow up.

The main limitation of our study is its external validity. Older couples that are willing to participate together may have better marital relationships and are open to behavior changes. This participants’ selection bias may not affect the study’s internal validity thanks to the randomized controlled study design, whereas its implication to broader older couples may need further examination.

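### The Reach indicator labelled representativeness in Table 3 is a coverage rate and cannot show whether enrolled couples resemble eligible ones

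*Protocol article*

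**What the plan says.** The Implementation evaluation section follows RE-AIM and gives Reach two components: "Reach will be revaluated by participation rate, and representativeness of participants". Table 3 then makes each one operational. Participation rate is "Enrolled couples /all couples being contacted". Representativeness is "Enrolled couples / all eligible couples registered in the system".

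The Recruitment section describes where the denominators come from: "community health care centers will first identify all potentially eligible participants from their case management system", and then "Community nurses will contact these patients and their spouses to inform them about the study".

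The Strengths & limitations section says "The main limitation of our study is its external validity". The reason given is that couples who agree to take part together may have happier marriages and be readier to change their habits.

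The Statistical considerations section plans a descriptive comparison of baseline characteristics, but between the two randomised arms.

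**The concern.** The text treats participation and representativeness as separate ideas, yet Table 3 measures both with a ratio that has enrolled couples on top. How many eligible couples enrolled and whether those who enrolled are like those who did not are different questions. A low coverage can go with a sample that mirrors the eligible population, and a high coverage with a selective one.

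At stake is what can be said about generalisability. The authors name external validity as their main limitation, and this is the one indicator labelled as bearing on it. If the ratio is reported under that label, readers may take it as evidence of resemblance, which it is not. This is not a detail left to a fuller document: the article states the definition, and the definition does not measure what it is named for.

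**Working it through.** The article states no figure to reproduce. The check sets the definitions side by side and adds a short illustration.

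**Inputs from the article**
- Planned enrolment: 194 couples (Sample size).
- Participation rate = enrolled / contacted (Table 3).
- Representativeness = enrolled / eligible and registered (Table 3).

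**Assumed, because the article does not give them**
- Number of eligible couples, N: 400, 600 or 1000.
- Share of men among all eligible patients: 50%.

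**Step 1: what enters each ratio.** The numerators are identical and only the denominators differ. Under the Recruitment section, nurses contact the patients whom the centres have identified from the case management system. The two denominators may therefore largely coincide, in which case the second ratio adds little even as a coverage measure. The article does not say how far they would differ in practice.

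**Step 2: range of the ratio.**
- 194/400 = 0.485
- 194/600 = 0.323
- 194/1000 = 0.194

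**Step 3: does it react to selection?** Take N = 600, so 600 − 194 = 406 eligible patients are not enrolled and 300 of the 600 are men.

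| | No selection on gender | Strong selection on gender |
|---|---|---|
| Men among 194 enrolled | 97 (50.0%) | 155 (79.9%) |
| Men among 406 not enrolled | 300 − 97 = 203 (50.0%) | 300 − 155 = 145 (35.7%) |
| Table 3 representativeness | 194/600 = 0.323 | 194/600 = 0.323 |
| Standardised difference | 0.00 | 1.00 |

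The standardised difference is (p1 − p2) / √{[p1(1 − p1) + p2(1 − p2)] / 2}. In the second column this is (0.799 − 0.357) / √[(0.161 + 0.230)/2] = 0.442/0.442 = 1.00. The Table 3 ratio is the same in both columns. The same holds for age or HbA1c, since neither enters the formula.

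**Step 4: is resemblance examined elsewhere?** The only stated comparison of baseline characteristics is between arms. It describes balance after randomisation and says nothing about couples who were eligible but did not enrol.

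**The case against.** **Coverage is not irrelevant.** The mean difference between enrolled and all eligible patients equals (1 − coverage) × (enrolled mean − non-enrolled mean). High coverage therefore caps how far the sample can depart from its source. This stands, but the cap is loose over the range shown: 1 − coverage is 0.515, 0.677 and 0.806 for N = 400, 600 and 1000. The second factor, which carries the selection, stays unknown. In the illustration, 0.677 × 0.442 = 0.299, which is the full excess of men among those enrolled (0.799 − 0.500).

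**Registry fields do not measure the feared selection.** The limitation concerns marital relationship and openness to change. Age, gender and last glucose value capture neither. This also stands. The comparison addresses the limitation only in part, though the present ratio shows nothing about who enrolled.

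**The consequence is small.** The article calls the trial a type 1 hybrid that primarily assesses health outcomes and explores implementation, and it already discloses the limitation. This stands and sets the weight of the point.

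**A stronger reading: that Maintenance merely repeats Effectiveness, so fading of the effect would go unseen.** A reader might infer this because Table 3 enters the same source for both domains, and Maintenance "will be measured as these treatment effect for long term (i.e. 1 year" while "Effectiveness will be indicated by the health outcomes listed in Table 2 above" without a time point. The documents do not support it:
- The entry equating the two sits in the data-collection column, so it says that the same measures are used, not that the estimates are identical.
- The intervention ends at month 3, so the 12-month visit falls about 12 − 3 = 9 months later and is a reasonable time to judge maintenance.
- HbA1c and SF-36 are measured at months 6 and 12, and self-care, medication adherence and physical activity in patients at months 3, 6 and 12. The planned repeated-measures models can show how the effect changes between visits.
- The two domains necessarily give one contrast only for measures taken at baseline and month 12 alone (blood pressure, BMI, waist–hip ratio, fasting glucose, lipids). For those, an effectiveness estimate at month 6 could not be computed.

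**Conclusion.** The point holds for the representativeness indicator alone. As defined, it is a second coverage ratio, unchanged by any mix of age, gender or glycaemic control among those enrolled, so it cannot show resemblance. That conclusion follows from the formula and does not depend on the assumed number of eligible couples, which serves only as illustration.

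Its weight is minor. One descriptive, exploratory indicator is affected. Randomisation, the primary analysis and the sample size are not. A reader might go further and infer that external validity would be fully assessed if the indicator were corrected, or that the trial's conclusions on efficacy are weakened as it stands. Neither follows. The selection that the authors fear is largely on traits that routine records are unlikely to hold, and the randomised comparison does not rest on this ratio.

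**What to change.** In Table 3, keep enrolled/eligible under Reach but name it coverage. Define representativeness as standardised differences between enrolled and eligible non-enrolled patients, on fields held in the case management system. Age, gender and latest fasting glucose or HbA1c are natural choices, since age and the glycaemic values are eligibility criteria and gender is a randomisation stratum. The article does not list the system's fields, so their availability should be confirmed with the centres.

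State that eligible here means eligible on registry information. Criteria such as literacy or the spouse's condition may be known only after contact.

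The cost is one aggregate or de-identified extract per centre, because those not enrolled have not consented. Recruitment had not begun when the article was written, so the extract could be specified alongside the screening list. The report should add that the comparison leaves marital quality and openness to change unexamined.
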